### Recruitment

The recruitment process will focus on Lithuanian-speaking students who are able to participate in in-person sessions on Vilnius University premises. The information about the study will be shared using different sources and different media outlets. First of all, the information will be sent out through emails, using student email accounts. Moreover, social media posts will be published on official social media accounts administered by the administration of higher education institutions, as well as student organizations of said institutions. Student organizations will also be asked to share information about the study in informal student social media groups. Paper posters will be put up in the common areas of higher education institutions. Finally, the representatives of the research team will seek to participate in various informational events at the higher education institutions and present in person the opportunity to participate in said study.

### Assignment of Interventions: Allocation

A random number generator (random.org) will be used to allocate participants randomly and equally to the study groups. A blocked randomization will be used as participants’ inclusion in the study will continue. Team members not involved in the participants’ screening and interviewing will generate a number and allocate participants to one of the two groups. A team member randomizing and allocating participants to one of the groups will have no information about the participant other than a generated user code.

### Implementation

Participants will be randomized and allocated to one of the two groups by team members who will not be involved in participants’ assessments and phone interviews. Randomized lists for allocation to two groups will be generated in advance with 3 batches of 20 blocked allocations and 3 batches of 10 blocked allocations at a time through a random number generator (random.org) by a team member not conducting preintervention assessments and phone interviews. During phone interviews, participants who indicated high levels of depression and suicidal ideation during screening will be informed about exclusion and provided with detailed information about available professional mental health services. After a participant is admitted to the study following a phone interview, a team member responsible for conducting phone interviews will provide a system-generated user code to the team member responsible for participants’ allocations, who will not have any other information about the participant. This allocator will then add the new participant to the existing randomized list of allocations to two groups in the sequential order of admittance to the study, which will assign them to one of the two groups.

### Assignment of Interventions: Blinding

Because of the nature of the intervention, neither participants nor therapists can be blinded to the intervention conditions. However, participants will not be explicitly told that the effect of the number of exposure sessions is tested. In the informed consent, participants will be informed that they will be asked to participate in up to 3 sessions of VR exposure, and after allocation to one of the groups, the participants will only be asked to participate in either 1 or 3 exposure sessions. Screening and posttreatment outcomes assessment will be done online, which will eliminate assessor bias. However, participants will be asked to again complete the primary outcome questionnaire in person right before the start of the exposure session and will complete some assessments during the session and right after.

### Interventions

Some studies have found that 1 session of VR exposure plus 4 weeks of an online program for public speaking anxiety was effective in reducing public speaking anxiety [25,41]. A previous meta-analysis comparing one session to several sessions of in vivo exposure for specific phobias did not find a difference in effectiveness between the two [32]. However, because of the specificity of VR exposure and public speaking anxiety, it is unclear how dividing the same amount of exposure tasks into three 1-hour-long sessions, including 3 tasks each (which is a more typical duration for a therapy session), instead of one 3-hour-long session including a total of 9 tasks, would affect the effectiveness of VR exposure for public speaking. After the exposure sessions, a 4-week online program to encourage the transition to in vivo exposure for public speaking will be part of both conditions.

The VR exposure intervention for public speaking anxiety chosen for this study is based on established tasks and negative belief testing used in traditional cognitive behavioral therapy and exposure-based interventions for public speaking anxiety. The effectiveness of this type of intervention has been confirmed in previous studies [42,43]. The intervention consists of two parts: a face-to-face VR exposure session, which has been adapted and modified from a previous study by Lindner et al [43], and a 4-week online intervention developed by Lindner et al [43]. Participants will be randomized into two intervention groups, either consisting of 1 or 3 VR exposure sessions, cumulatively consisting of the same number of same-length exposure tasks. Both groups will participate in a 4-week online transition intervention after VR sessions.

### VR Exposure Sessions

At the beginning of the VR exposure session, all participants will be presented with psychoeducation on public speaking anxiety and the principles of exposure tasks. Over the course of the session, participants will perform 9 exposure tasks that will last from 1 minute to 3 minutes each. Two of these 9 speaking tasks will have 1 and 2 additional minutes for preparation before the speech. During exposure tasks, participants will use a VR headset to virtually stand before varying-sized audiences and distances from the crowd (specific audiences will be consistently ascribed to specific tasks). Tasks will vary in difficulty and will include participants having to count backward, come up with as many words as possible starting with the same letter, talking about themselves, their interests, achievements, their fear of public speaking, and preparing and giving a speech on one of the several controversial topics like the admission of migrants, euthanasia, abortion, etc. Concerning the controversial topics, participants will be allowed to pick one out of a list of topics to reduce unnecessary discomfort or will be able to refuse to complete the task, based on the voluntary participation condition described in informed consent. Similar to Lindner et al [25,43] in-session procedure, before each task, participants will be asked to report their level of distress, identify their negative beliefs/expectations about each public speaking task, and evaluate the chances of their negative expectations to come true. Their performance of the task will be recorded. After each task, participants will rate the current level of distress, the highest level of distress during the task, the perceived quality of their performance, and the level of presence they felt in the VR environment. Subsequently, participants will be invited to listen to the recording of their speech and instructed to imagine that they are listening to this speech from a third-person perspective while in the same audience. Afterward, they will again be prompted to evaluate the speech quality and the degree to which their negative beliefs or expectations were confirmed. At the end of the session, participants will be asked to provide feedback on the convenience of the 3-hour 1-session format, and they will be given information about the importance of the transition to in vivo exposure in their daily lives and encouraged to use online intervention to help them with the in vivo exposure transition.

In the group of the 3 VR exposure sessions, the same procedure will be applied, except that the same exposure tasks in the same order will be divided into the 3 sessions (first session: tasks 1‐3; second session: tasks 4‐6; third session: tasks 7‐9). All 3 sessions will be held over a period of 2 weeks. Psychoeducation will be provided only in the first session, and information about the importance of transition to in vivo exposure as well as an assessment of the convenience of the 3-session format will be done only in the last session. Exposure sessions will be conducted by trained clinical and health psychologists and psychology master’s students supervised by experienced psychologists.

### Online Intervention

A self-guided online intervention that has been developed and studied in previous VR exposure studies by Lindner et al [25,43] will be used. The intervention was adapted and translated into Lithuanian in collaboration with the intervention developers. One week after the last VR session, participants will be invited to complete a postexposure assessment, after which they will be able to start the online transition intervention.

The online intervention consists of 4 modules, each available consecutively over the course of 4 weeks. The modules reiterate important psychoeducational information and focus on encouraging the participants to plan and carry out public speaking in vivo exposure tasks. They are asked to complete 4 public speaking tasks per week, for example, to attend an event or presentation and ask questions, to do a public presentation, or to pretend to speak on the phone on a bus or train [43]. Each of the 4 modules is designed to work on important aspects of overcoming public speaking anxiety: the first module introduces the transition from VR exposure tasks to public speaking in everyday life, the second module focuses on safety behaviors, the third module concentrates on catastrophic beliefs, and the fourth module covers the planning for the future and relapse prevention [43]. If participants have any questions about the tasks of the online program during these 4 weeks, they will be able to contact the program psychologist through the online program’s secure messaging system. A so-called therapist support-on-demand approach was chosen for this study.

### Criteria for Discontinuing or Modifying Allocated Interventions

It is in the nature of the exposure tasks that participants are expected to experience some level of distress, and it is important not to discontinue exposure because of experienced anxiety. However, if participants experience significant distress and, after careful consideration and discussion, participants still do not feel comfortable continuing, exposure tasks will be suspended. In this case, emotional support will be provided by the therapist conducting the session. Participants might be referred for further psychological help to psychological services. Intervention may be discontinued if participants express significant discomfort and wish to discontinue for other reasons, for example, because of motion sickness. All cases of discontinuation and the reasons would be recorded and reported. During the online intervention, participants will be instructed to notify the research staff in case of a significantly deteriorating psychological condition. In that case, a trained psychologist from the team will conduct a clinical assessment via telephone interview. Based on the evaluation, the participant may be referred to alternative psychological services.

### Strategies to Improve Adherence to Interventions

To improve adherence to the intervention, participants will be contacted by phone, first discussing whether participants will be able to participate in the exposure sessions, as well as getting confirmation that they will be able to participate in the 4-week online intervention. If patients cancel or do not show up to their scheduled exposure sessions, they will be contacted via phone to discuss possible barriers and, if possible, schedule a new suitable appointment for a session. However, if they express the desire not to participate in the study, they will be able to do so freely. Finally, participants who do not log into the online intervention will also be contacted to provide encouragement and technical support for them to be able to participate.

### Outcome Measures

#### Primary Outcome Measures

To assess public speaking anxiety and to track the changes after the intervention, the PSAS [44,45] will be used. Assessment with the PSAS will take place at preintervention (during participant selection), at the beginning of the first exposure session, postintervention at week 1, after finishing the online program at week 5, and two follow-ups at 3 months and 12 months after finishing the online program. The PSAS score during online eligibility screening will be the baseline measure; change in score from baseline will be assessed. The scale consists of 17 self-report statements (eg, “giving a speech is terrifying”) measured on a Likert-type scale ranging from 1 “not at all” to 5 “extremely.” This scale measures 3 components of public speaking anxiety: cognitive (8 items), behavioral (4 items), and physiological (5 items). The overall score on the scale ranges from 17 to 85. A higher score indicates higher levels of experienced public speaking anxiety. Initial assessment of the factor structure and reliability of the Lithuanian version of PSAS was conducted with 227 participants aged 18‐25 years. The scale showed good internal consistency (α=.93), while factor structure analysis supported the use of the total score (root-mean-square error of approximation [RMSEA]=0.07), suggesting it is suitable for use in the young adult sample [45].

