### Participants and Eligibility Criteria

Participants will be eligible for the program if they meet the following inclusion criteria: (1) young adults aged between 18 and 30 years; (2) students pursuing higher education; (3) a significant level of public speaking anxiety (Public Speaking Anxiety Scale [PSAS] score of 60 or above); (4) access to a computer and internet access for the duration of the study; (5) can understand, write, and speak Lithuanian; and (6) able to participate in 1 or 3 in-person intervention sessions and are able to devote the time to participate in a 4-week online program following the intervention sessions. Participants will be excluded from the study if (1) they have a history of seizures or epilepsy; (2) they have other significant medical conditions that would prevent them from participating in the program; (3) they have high levels of depression (Patient Health Questionnaire-9 [PHQ-9] rating of 15 and above and mentions of suicidal ideation) or other significant psychiatric conditions that would interfere with participation in the program; (4) they have a tendency to have extreme motion sickness reactions or a history of negative physical reactions to VR experiences or difficulty with or lack of stereoscopic vision; (5) they are currently involved in other psychological interventions such as psychological counseling or psychotherapy; (6) they use psychoactive drugs, unless stable for 3 months; or (7) they are currently participating in other programs aimed at reducing public speaking anxiety.

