### Data Collection and Management

#### Plans for Assessment and Collection of Outcomes

Data will be collected at prerandomization, during the sessions, 1 week after the last session before starting the online intervention, after 4 weeks of online intervention, and then at 3- and 12-month follow-ups. Baseline assessment, posttreatment assessment, and follow-up assessments will be completed online. At the beginning of the exposure session, participants will fill in the primary measure again using a paper-and-pencil questionnaire format, and in-session assessments will be filled in the paper session protocol as well. All questionnaires will be based on participants’ self-report. The full timeline of assessments is provided in Table 1.

**Table 1. T1:** Schedule of enrollment, interventions, and assessments for the randomized controlled trial comparing 1-session and 3-session of virtual reality (VR) exposure therapy for public speaking anxiety among young adults.

Assessment/activity	Screening		Postrandomization						Follow-up	
	*t* _−1_ ^a^	*t* _0_ ^b^	*t* _1_ ^c^			*t* _2_ ^d^	*t*_3_-*t*_6_^e^	*t* _7_ ^f^	*f* _1_ ^g^	*f* _2_ ^h^
			Pre-VR exposure	During exposure	Post-VR exposure				3 months	12 months
Informed consent	✓		✓							
Demographic data	✓									
LSAS-SR^i^	✓					✓		✓	✓	✓
PSAS^j^	✓		✓			✓		✓	✓	✓
BFNE^k^	✓					✓		✓	✓	✓
PHQ-9^l^	✓									
IPQ^m^					✓					
In-session assessments: SUDS^n^, catastrophic belief expectancy, quality of performance, single-item presence measure				✓						
Evaluation of intervention format (1-session or 3-session)					✓					
Treatment satisfaction, negative effects								✓		
VR exposure therapy				✓						
4-week online program							✓			
Eligibility criteria	✓	✓								
Treatment expectancy	✓									
Treatment engagement							✓			

a *t*_−1_: online eligibility screening and control data collection (baseline).

b *t*_0_: further screening during telephone interview.

c *t*_1_: face-to-face VR exposure intervention delivery, either via one 3-hour session or via three 1-hour sessions.

d *t*_2_: outcome assessment 1 week after completion of face-to-face VR exposure intervention, either after one 3-hour session or after three 1-hour sessions (first primary endpoint).

e *t*_3_-*t*_6_: 4 weeks of online program with new tasks and materials available weekly.

f *t*_7_: outcome assessment after finishing the 4-week online program or equivalent time if the online program was discontinued (second primary endpoint).

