### Statistical Analysis

The primary outcome will be a change in PSAS scores from baseline to posttreatment assessment (two primary endpoints: *t*_2_ and *t*_7_), as well as during follow-up assessments in both intervention groups. Secondary outcomes will be changes in secondary outcome measures from baseline to posttreatment and follow-ups. Repeated measures within-between ANOVA and effect sizes will be used to assess and compare outcomes within and between groups. The reliable change index (RCI) will be used as a supplementary analysis to analyze individual outcomes following intervention. No interim analyses or formal stopping rules were planned because this intervention is considered low-risk and is not expected to cause any harm to the participants. Regression analysis will be used to test the extent to which the level of anxiety and other psychological states measured by primary and secondary measures during baseline, sense of presence (IPQ at the end of the treatment), age, and gender, and user experience rated by participants predict the efficacy of the intervention. Single-item sense of presence after each task and user experience ratings of the format will be used for further exploratory purposes. In order to handle protocol nonadherence and missing data, it is planned that intention-to-treat will be the primary analysis approach, supplemented by additional per-protocol analysis. As recommended by the CONSORT (Consolidated Standards of Reporting Trials) guidelines, both analyses will be performed and reported for primary outcomes [57], allowing comparison of the effects of both approaches. Multiple imputation techniques will be used to fill in missing data.

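### The screening PSAS that admits participants is also the baseline for change, so within-arm effects, and probably the reliable-change rates, include regression to the mean

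*Protocol article*

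**What the plan says.** Under Participants and Eligibility Criteria, the protocol article requires "a significant level of public speaking anxiety (Public Speaking Anxiety Scale [PSAS] score of 60 or above". Under Primary Outcome Measures it fixes the start point for change: "The PSAS score during online eligibility screening will be the baseline measure; change in score from baseline will be assessed". Table 1, footnote a, agrees, describing the first time point as "online eligibility screening and control data collection (baseline".

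The Statistical Analysis section builds on that baseline:

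- Outcome: "The primary outcome will be a change in PSAS scores from baseline to posttreatment assessment".
- Comparisons: "Repeated measures within-between ANOVA and effect sizes will be used to assess and compare outcomes within and between groups".
- Individual outcomes: "The reliable change index (RCI) will be used as a supplementary analysis to analyze individual outcomes following intervention".
- Prediction: "Regression analysis will be used to test the extent to which the level of anxiety and other psychological states", as measured at baseline, predict how well the intervention works.

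No other baseline is named for any of these. A second pre-treatment PSAS is taken: "At the beginning of the exposure session, participants will fill in the primary measure again using a paper-and-pencil questionnaire format". No analysis is assigned to it. The Limitations section confirms that there is no inactive control group, and it does not mention regression to the mean.

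**The concern.** A single PSAS reading is part stable level and part occasion-to-occasion error. Admitting people because that reading reached 60 favours those whose error was upward on the day, and their next reading is lower on average with no treatment at all. When the gate reading is also the start point for change, that fall is counted as improvement. With no untreated arm, nothing in the design separates the two.

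Three secondary outputs are exposed: within-arm effect sizes, the share of participants called reliably improved, and any statement that more anxious participants benefit more. In the last case the baseline enters on both sides, as predictor and, with a minus sign, inside the change score.

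**Working it through.** **The plan's own figure.** The article gives no figure on this point. Its sample size reproduces: for the between-factors test, λ = f²·N·m / (1 + (m−1)ρ) = 0.0625 × 86 × 3 / 2 = 8.06, giving power 0.8015 at N = 86 and 0.792 at N = 84. It is unaffected by what follows.

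**Inputs from the article.** Cut-off 60; scale range 17-85; internal consistency α = .93; 37 of 101 screened met the criteria and were randomized (Results, Recruitment).

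**Inputs not in the article, assumed.** Mean and SD of PSAS among those screened, and its retest correlation r. All 37 randomized scored 60 or above, so at least 37/101 = 37% of those screened did. A normal distribution with mean 50 and SD 13 puts only about 23% at 60 or above (whole-number scores), and 37 or more of 101 then has probability of about 0.002. A mean of 55 puts 34% (SD 11) to 36% (SD 13) there, which is compatible. I used means 55-65, SD 11-13 and r of 0.7, 0.8 and 0.9.

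**Closed form, one case (mean 55, SD 13, r = 0.8).** With whole-number scores the cut is at 59.5, so z = 4.5/13 = 0.346. The ratio of normal density to upper tail is 1.031, and the selected mean is 55 + 13 × 1.031 = 68.4. Expected fall with no true change: (1 − r)(68.4 − 55) = 0.2 × 13.4 = 2.7 points. The selected SD is about 6.7, so the spurious within-arm effect is 2.7/6.7 = 0.40 SD.

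**RCI threshold.** 1.96 × SD × √(2(1 − .93)) = 9.5 points at SD 13 and 8.1 at SD 11, taking the SD of the unselected screened population (an assumption).

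**Simulation with no true change** (independent errors between occasions, scores rounded and limited to 17-85, selection at 60). Ranges are over the assumed means and SDs:

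| r | Spurious fall, points | Falsely improved | Falsely deteriorated | Falsely improved, session-1 baseline | Correlation of screening PSAS with change |
|---|---|---|---|---|---|
| 0.9 | 0.6-1.4 | 5-7% | 2-3% | 4-5% | −0.12 to −0.16 |
| 0.8 | 1.1-2.7 | 13-19% | 5-7% | 10-12% | −0.17 to −0.22 |
| 0.7 | 1.7-4.0 | 19-28% | 7-10% | 15-17% | −0.21 to −0.27 |

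Nominal is 2.5% in each direction. With the session-1 PSAS as start point, the spurious mean change is 0.0 in every setting and improved and deteriorated rates are equal.

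**Why session 1 does not restore 2.5%.** At r = 0.8 a difference of two readings has SD √(2 × 0.2) = 0.632 population SDs, while the threshold is 1.96 × √0.14 = 0.733. That is 0.733/0.632 = 1.16 standard deviations of change, with a tail of about 12%. This part comes from using α = .93 where retest reliability is lower, not from selection.

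**Prediction.** With no true effect, the expected post score given baseline has slope r, so change has slope r − 1: −0.1, −0.2 and −0.3. With baseline PSAS in the model, replacing change by the post score adds exactly 1 to the baseline coefficient and leaves every other coefficient unchanged.

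**Between arms.** Both arms pass the same gate before randomization and regress equally in expectation. A null simulation gave a between-arm difference of 0.003 points.

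**The case against.** The strongest case against is about weight. The trial's question is the randomized comparison, which is untouched. RCI is labelled supplementary, and the Limitations section already says the study does not test against no treatment. That stands, and it confines the point to secondary claims. It does not remove it, because the within-arm figures will still be reported and the stated caveat does not cover this mechanism.

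Several stronger readings are tempting and are not supported:

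- A reader might infer that the RCI is stated to use the screening score and that efficacy is defined as change. The Statistical Analysis section says neither. Both follow only from the general baseline definition and the form of the primary outcome, and an analysis plan not shown could settle them.
- A reader might assume a screened mean of 45-50 and so a larger artefact. The 37 of 101 makes that implausible.
- A reader might take the 0.5 under Sample Size as a retest coefficient and conclude that baseline and change correlate −0.50 by construction. It is a planning correlation across treatment, and the equal variances this needs conflict with a sample selected on baseline.
- A reader might conclude that all predictor results are distorted, or that within-arm improvement is wholly artefact. Only the baseline PSAS coefficient is affected in this way, and nothing here says the true effect is nil.

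The remedy also has fair objections. The session-1 score is on paper, after allocation, possibly raised by anticipatory anxiety, and missing for those who never attend. Most of the excess RCI error at r = 0.8 would remain.

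**Conclusion.** The point holds in a limited form. The gate score is the stated baseline, so within-arm effect sizes include regression to the mean. The RCI improved rates do too if they follow the same baseline. If efficacy is a change score, the baseline PSAS coefficient is negative under no influence of severity. The between-arm comparison is not biased.

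The size rests on assumed screening values and on retest reliability, which the article does not give: small if r is near 0.9 or above, material at about 0.8 or below. It merits correction as a secondary matter.

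**What to change.** 1. Keep the screening PSAS as baseline or covariate for the between-arm comparison.
2. Report within-group effect sizes and RCI rates also from the PSAS taken at the start of the first session, beside the screening-based figures. Label this post hoc, since the Limitations section says the team has already worked with the data. State that the screening-based figures include regression to the mean.
3. Do not interpret the coefficient of baseline PSAS on change as prediction of benefit. Modelling the post score instead does not make that coefficient interpretable as benefit either. Coefficients of other predictors need no change once baseline PSAS is in the model.

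Cost: no new data, a short reanalysis and a paragraph of text; the Limitations section leaves final statistical decisions to the results reports. Downside: given its mode, timing and missingness, the session-1 score should serve within-arm analyses only. It also does not remove the RCI error from using α = .93 where retest reliability is lower, which the report should say.
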